## 6.2 Patients with Bipolar Mania

Inclusion criteria: ① meeting the diagnostic criteria by the fifth edition of the Diagnostic and Statistical Manual of Mental Disorders (DSM-5) and currently during a manic episode; ② inpatients in Shanghai Mental Health Center; ③ clinical indications of receiving convulsive treatment, such as severe psychomotor excitement or retardation, attempts of suicide, being highly aggressive, pharmacotherapy intolerance, and ineffectiveness of antipsychotics; ④ age between 18 and 55 years old; ⑤ moderate to severe manic symptoms with scores of Young Manic Rating Scale (YMRS)  $\geq 10$ ; ⑥ Written informed consent.

Exclusion criteria: ① comorbidity with other mental disorders by DSM-5; ② with unremovable metal implants; ③ a laboratory abnormality with an impact on the efficacy of treatments or safety; ④ severe physical diseases (stroke, heart failure, liver failure, neoplasm, or immune deficiency), a laboratory abnormality with an impact on the efficacy of treatments or safety; ⑤ Alcohol or substance dependence in the 30 days prior to the start of the trial or in the 6 months prior to the trial; ⑥ failure to respond to an adequate trial of ECT; ⑦ being or intending to get pregnant during the study; ⑧ other conditions that investigators consider to be inappropriate to participate in this trial.

## 7. Sample Size

Due to the lack of previous MST study as an adjunctive treatment for bipolar mania, we estimated based on previous ECT study. The following formula was applied with  $\alpha=0.05$ ,  $\beta=0.80$ ,

$$n = 2\pi(1 - \pi) \left[ \frac{(u_{1-\alpha} + u_{1-\beta})}{\delta} \right]^2$$

The sample size is 30 for ECT and MST group, respectively.

## 8. MST and ECT Procedures

General anesthesia was administered for each participant before each ECT/MST

session by administering propofol (1.82-2.44mg/kg) and etomidate (0.21-0.3mg/kg). The succinylcholine (1mg/kg) was used for muscle relaxation to prevent fractures and other injuries, and the atropine (0.5mg) was used for reducing respiratory secretions. After each ECT/MST session, patients stayed under observation for half an hour and were not allowed to eat until two hours later.

**MST Procedure:** Patients completed 2 or 3-session MST on alternate days every week and achieved 8-10 sessions accumulatively within 4 weeks. MST was administered using the MagPro X100 device with a twin coil (Twin Coil-XS, MagVenture A/S, Denmark) placed and centered on the vertex. The intensity was at 100% device output with 75 Hz frequency. The duration of magnetic stimulations was determined by a titration method until a proper seizure (seizure duration  $\geq 15$  s) was generated. The duration started from 4 s and was increased by 4 s or 8 s up to a maximum of 20 s.

**ECT Procedure:** Patients completed 2- or 3-session MECT on alternate days weekly and accumulated 8-10 sessions within 4 weeks. ECT was performed using the Thymatron System IV device (Somatics, USA) with electrodes placed over the bilateral temporal cortex. The electrical stimulation wave width was at 1.0 ms. The energy of electrical stimulation was determined according to the patient's (age  $\times 0.8 \times 100\%$ ). The energy percent was increased by 5% until a proper seizure (seizure duration  $\geq 25$  s).

**EEG Recording:** During each MST/ECT session, patch electrodes were placed in the bilateral frontal regions to record electroencephalogram (EEG). The epileptiform discharge times induced by MST/ECT were recorded as the effective seizure duration.

## **9. Outcome Measures**

### **9.1 Primary outcomes**

Designated qualified psychiatrists assessed all patients' symptoms before and after the entire MST and ECT treatments. Manic symptoms were assessed by YMRS. The reduction rate of YMRS total scores was used as the primary outcome. The response is defined as a  $>50\%$  reduction of YMRS total scores compared to the baseline.

### **9.2 Secondary outcomes**

#### **9.2.1 Other clinical outcomes**

Before and after the MST/ECT treatments, depressive symptoms were assessed

using the Montgomery-Asberg Depression Rating Scale (MADRS) and clinical outcome using CGI.

### **9.2.2 Neurocognitive outcomes**

Neurocognitive function were evaluated using the Repeatable Battery for the Assessment of Neuropsychological Status (RBANS) [2]. We used the Chinese version of RBANS, which has good reliability and validity [3], consisting of 12 tasks for five cognitive domains: Immediate Memory (IM), Visuospatial / Constructional (V/C), Language, Attention, and Delayed Memory (DM). A trained staff operated the RBANS assessment. Some participants did not complete the RBANS assessments due to emotional instability and behavioral incooperation in the acute phase. MADRS total scores, RBANS total scores, and scores of each RBANS cognitive domain were secondary outcomes.

### **9.2.3 CI outcomes**

Magnetic stimulation is applied to the left motor cortex through TMS and surface electromyography (EMG) electrodes are placed at the the abductor pollicis brevis muscle position. Motor-evoked potentials (MEPs) are recorded. Multiple CI measures were obtained.

### **9.2.4 GABA measures by MRS**

Using Siemens 3T Verio magnetic resonance imaging (MRI) system, the MEGA-PRESS sequence is employed with parameters set as follows: TR (repetition time) = 2000ms, TE (echo time) = 69ms, and an average of 128 acquisitions. The data is collected with the region of interest in the frontal lobe, and reconstruction is performed in a plane perpendicular to the splenium of the corpus callosum, with voxel size set at 30mm \* 30mm \* 30mm.

### **9.2.5 fMRI measures**

Before and after the ECT or MST treatment, MRI data will be collected at the Shanghai Mental Health Center using a Siemens 3T MRI scanner, including T1, T2, and resting-state fMRI data.

For T1-weighted images, the magnetization-prepared rapid gradient-echo (MP-RAGE) sequence is employed with a repetition time (TR) of 1800ms, echo time (TE) of 3.4ms, inversion time (TI) of 1100ms, flip angle (FA) of 7 degrees, field of view (FOV) of 256mm, voxel size of 1mm\*1mm\*1mm, and axial continuous scanning of 176 layers. The GRAPPA algorithm is used with a parallel imaging factor of 2, and the

entire scanning process lasts for 3 minutes and 57 seconds.

For T2-weighted images, the sequence has a repetition time (TR) of 3200ms, echo time (TE) of 224ms, FOV of 256mm, voxel size of 1mm\*1mm\*1mm, and axial continuous scanning of 176 layers. The GRAPPA algorithm with a parallel imaging factor of 2 is applied, and the scanning process takes 4 minutes and 43 seconds.

For resting-state functional images, the sequence has a repetition time (TR) of 6000ms, echo time (TE) of 30ms, flip angle (FA) of 90 degrees, FOV of 192mm, 60 measurements, voxel size of 2mm\*2mm\*2mm, and axial continuous scanning of 67 layers. The entire scanning process for resting-state functional images lasts for 6 minutes and 32 seconds. During scanning, all participants are instructed to keep their eyes open without any specific thoughts.

## 10. The Study Flow Chat

[figure not shown]

Figure 1. The study flow chat

## 11. Exit (Dropout) Criteria

During the trial, if the following conditions occur, the researcher is responsible for terminating the subject's continued participation in the trial (excluding them).

Subsequently, a detailed explanation and assessment of the termination reason, date, and the clinical process leading to the event should be recorded on the case report form. Subjects are free to withdraw (dropout).

(1) As determined by the investigator, the trial cannot continue due to adverse events or abnormal laboratory test values; (2) The subject want to withdraw from the trial; (3) Significant protocol violations (including those deemed non-compliant by the investigator); (4) Other situations where the investigator deems it inappropriate or difficult to continue the trial.

Subjects have the right to withdraw from the trial at any time without providing any reason. If a subject decides to withdraw from the trial, the researcher should inquire about the reasons to the extent possible and document them in the source documents and case report forms. When a subject withdraws from the trial prematurely, an exit assessment must be conducted.

## **12. Risk and Its Control**

Although there may be risks and adverse reactions during the process of ECT/MST treatment, the adverse reactions are relatively few and mild, and serious complications are rare. Possible accidents and adverse reactions include: (1) Individual patients may be insensitive to muscle relaxants, leading to accidents such as fractures and joint dislocations; (2) Some patients may experience reversible headaches, nausea, muscle pain, and recent memory disturbances in the short term. Anesthetic accidents and complications may include: (1) Vomiting, aspiration, and laryngospasm may occur during anesthesia treatment; (2) Patients may be allergic to anesthesia drugs; (3) Due to individual differences, patients may experience slow metabolism of anesthetic drugs, leading to delayed recovery of spontaneous breathing or even requiring tracheal intubation; (4) Anesthesia may induce and exacerbate pre-existing diseases, potentially causing disruptions in heart, brain, and respiratory functions.

We will implement several measures to reduce these accidents and adverse reactions, such as: (1) Strict fasting within 6 hours before the procedure, and no water intake within 3 hours before the procedure; (2) Removal of dentures and all kinds of accessories before the procedure; (3) After the procedure, the patient must remain in the treatment room until fully awake and obtain permission from the doctor to leave. A healthcare professional or a guardian responsible for the patient's medical care must accompany the patient; (4) Eating is allowed 2 hours after the procedure; (5) Within 12

hours after the end of general anesthesia, activities such as climbing, driving, and making important decisions should be avoided.

### **13. Recording, Reporting, and Handling of Adverse Events**

If any clinically significant findings are discovered in laboratory tests, vital signs, electrocardiograms, and other examinations, the investigator or assistant researcher should record them on the "Pre-existing Conditions and Adverse Events" page of the case report form. For findings that have clinical significance and can lead to a specific diagnosis, the diagnosis should be documented as an adverse event. If a diagnosis cannot be made, the clinical significance should be determined by the investigator, and findings deemed to have clinical significance should be recorded as adverse events.

After the investigator discovers a serious adverse event, they must report it to the designated personnel within 24 hours through a method approved by the Principal Investigator (PI). Following a telephone report, the investigator must promptly complete and send the study-specific Serious Adverse Event Record Form for the following events: death; initiation of hospitalization or prolongation of hospital stay; life-threatening situations (immediate risk of death); persistent or significant disability or functional impairment; congenital anomalies or birth defects; any event that the investigator deems significant for any reason.

Accurately complete the Adverse Event Record Form during the trial, documenting the occurrence time, severity, duration, measures taken, and outcome of adverse events.

In the event of a serious adverse event, immediate necessary measures must be taken to ensure the safety of the subjects. All adverse events should be thoroughly investigated, with detailed documentation of the process and outcomes of the intervention, until a satisfactory resolution or stabilization of the condition is achieved. In the case of laboratory abnormalities, tracking should continue until normalization. Follow-up methods can be chosen based on the severity of the adverse reaction and may include hospitalization, outpatient visits, home visits, telephone follow-ups, correspondence, or other forms.

Any serious adverse reaction events occurring during the trial must be reported immediately to the local or principal medical ethics committee and the sponsor. The "Serious Adverse Event Report Form" should be completed. Notify the units and contacts listed in the informed consent form. Follow-up for unresolved adverse events:

350 All adverse events should be tracked until a satisfactory resolution or stabilization of  
351 the condition is achieved.

## 352 **14. Data Management and Statistical Analysis Plan**

### 353 **14.1 Data Management**

354 The case report forms are uniformly organized and kept by dedicated personnel.  
355 They are only taken out when data entry personnel are inputting and verifying data, and  
356 are promptly returned to their original state after completing these tasks. During the  
357 project implementation, a dedicated database is established to track various information  
358 about the study subjects and record adverse events. A dedicated person is responsible  
359 for the security management of the database and utilizing it for research quality control.

### 360 **14.2 Statistical Analysis Plan**

361 We will use SPSS for statistical analysis, employing statistical methods such as t-  
362 tests, analysis of variance, and correlation analysis based on the data types and  
363 distribution characteristics. For the MRS data, LC-Model will be utilized. After  
364 preprocessing, resting-state fMRI data will be analyzed using software packages such  
365 as REST and GIFT.

366 (1) Baseline comparisons: To compare the differences in neurocognitive function,  
367 CI indicators, and resting-state fMRI measures between the MST group, ECT group  
368 and healthy control group; To explore the correlation between CI indicators and GABA  
369 levels detected within each group.

370 (2) Longitudinal comparisons: Compare the longitudinal changes of clinical,  
371 neurocognitive and CI measures before and after ECT and MST interventions.

372 (3) fMRI: the medial prefrontal cortex within the default mode network (DMN)  
373 will be chosen as a seed to calculate its functional connectivities the posterior cingulate  
374 gyrus, precuneus and the bilateral inferior parietal lobules. We hypothesize that patients  
375 with bipolar mania may show enhanced connectivity within the DMN, and this  
376 connectivity will be improved after MST or ECT intervention.

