## **4.3 The Mechanism of ECT and MST Treatments**

Although ECT treatment has a history of more than eighty years, the therapeutic

mechanisms for treating manic episodes are far from clear. Initiating this project provides us with an opportunity to investigate the biological mechanisms of ECT and MST interventions. Evidence in this regard will support the future optimization of ECT and MST treatment techniques.

We propose a hypothesis that MST may improve GABA-mediated cortical inhibition (CI) deficits in patient. ECT may significantly increase the seizure threshold in patients by inducing seizures, thereby strengthening cortical inhibitory function [11]. A typical ECT treatment course usually involves 8-10 sessions within approximately a month. As the number of ECT treatments accumulates, the seizure threshold of patients continues to rise. The required stimulus intensity to induce seizures also gradually increases. In comparison to the initial treatment, the intensity required for seizures in the final treatment session often needs to be increased by 50% to 100%.

The CI function can be assessed using TMS, reflecting the inhibitory GABA-mediated cortical response [12]. Research on CI function in patients with schizophrenia has yielded relatively stable results by cortical silent period (CSP), short-interval cortical inhibition (SICI), and intracortical facilitation (ICF). Previous studies have demonstrated reduced CI function in BD patients, reflecting an inhibitory deficit [13].

CI can also be assessed using magnetic resonance spectroscopy (MRS) to identify changes in in-vivo GABA levels in BD individuals [14,15]. However, there is currently a lack of longitudinal reports on changes in GABA levels in BD patients related to ECT or MST interventions. We believe that relying on TMS-derived cortical inhibition indicators and GABA levels detected through MRS technology will provide reliable evidence for mutual validation.

CI function can also be assessed in vivo by magnetic resonance spectroscopy (MRS), reflecting the GABA levels. Previous MRS studies have suggested altered GABA levels in BD individuals [14,15]. However, there is currently a lack of longitudinal studies reporting changes in GABA levels in BD related to ECT or MST. We hypothesize that CI indices measured by TMS and GABA levels measured by MRS will provide more evidence for the underlying mechanism of ECT and MST treatments.

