#### **6.1 Healthy controls**

Healthy controls will only participate in baseline cognitive function assessment (rBANS), cortical inhibition (including TMS and MRS detection), and resting-state fMRI assessments. They will not receive MST or MST treatments and not participate in follow-up assessments.

The healthy control will give written consent before participating in the assessments. They will be matched with the patient group in terms of sex, age (between

18 and 55 years), years of education, and socio-economic status. In addition, they will be screened to exclude an occurrence of psychiatric disorders by the DSM-5 diagnostic criteria. They have no family history of psychiatric disorders, no history of substance dependence, are not currently taking any medication, and do not have any concurrent major physical illnesses.

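### Section 14.2 names only unadjusted methods for the baseline control comparisons and the exploratory CI-GABA correlation, although the matching variables are available for adjustment

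*Protocol*

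**What the plan says.** Protocol section 6.1 says of the 30 healthy controls: "They will be matched with the patient group in terms of sex, age", and adds years of education and socio-economic status. The match is to the patient group as a whole; no pairs are described. Patients and controls both range from 18 to 55 years.

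Protocol section 14.2 gives the methods. The sentence opens "We will use SPSS for statistical analysis, employing statistical methods such as t" and runs on "tests, analysis of variance, and correlation analysis based on the data types and" distribution. Item (1) then lists the baseline comparisons: neurocognitive function, "CI indicators, and resting-state fMRI measures between the MST group, ECT group" and the controls. It also sets out an exploratory analysis: "To explore the correlation between CI indicators and GABA" within each group. No covariate, ANCOVA or partial correlation is named for any of these, and none is ruled out.

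Protocol section 4.3 gives the background to the CI and GABA measures. It expects that relying on both kinds of measure "will provide reliable evidence for mutual validation".

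**The concern.** The design takes trouble over four variables and the analysis section then makes no visible use of them. Two consequences follow if the named methods are applied in their plain form.

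- **Precision.** Group matching makes the average age, sex mix, education and socio-economic status similar across groups. It does not remove the spread of these variables inside each group. Where they predict cognition, CI or connectivity, that spread stays in the residual variance, and the standard error of each contrast with the controls is larger than it need be.
- **Age in the CI-GABA correlation.** The correlation is computed within a group whose members may be 18 or 55. If CI and GABA each vary with age, they will correlate with one another even when they are unrelated among people of the same age. The induced correlation is positive or negative according to the directions of the two age relations.

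At stake are the power of the secondary comparisons with the controls and the reading of one exploratory mechanistic result.

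**Working it through.** The protocol states no figure for these analyses, so there is none to reproduce. The stated 30 per arm in section 7 does not bear on the point.

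**Inputs from the protocol**
- 30 ECT and 30 MST patients (section 7) and 30 controls (section 6).
- Age 18 to 55 in patients and controls (sections 6.1 and 6.2).

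**Inputs assumed, because the protocol gives none**
- R², the share of within-group variance explained by the matching variables: 0.10 to 0.30.
- The correlation of age with CI and with GABA, taken as equal in size: 0.2 to 0.5.
- Two-sided alpha 0.05 and power 80%.

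**Step 1: precision of the contrasts with the controls**

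Unadjusted SE in SD units = sqrt(1/n1 + 1/n2). With adjustment it is multiplied by sqrt(1 − R²). The detectable difference is (1.96 + 0.84) × SE = 2.80 × SE.

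- 30 v 30 (one treatment arm against controls): SE = sqrt(2/30) = 0.258; detectable difference 0.72 SD.
- 60 v 30 (both arms pooled): SE = sqrt(1/60 + 1/30) = 0.224; detectable difference 0.63 SD.

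| R² (assumed) | sqrt(1 − R²) | 30 v 30 | 60 v 30 | Equivalent gain in participants, 1/(1 − R²) − 1 |
|---|---|---|---|---|
| 0 | 1 | 0.72 | 0.63 | 0% |
| 0.10 | 0.949 | 0.69 | 0.59 | 11% |
| 0.20 | 0.894 | 0.65 | 0.56 | 25% |
| 0.30 | 0.837 | 0.61 | 0.52 | 43% |

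The 30 v 30 column is the relevant one, because section 14.2(1) lists MST, ECT and controls as three groups. The pooled column applies only if the patient arms are combined. The table ignores the few degrees of freedom spent on covariates.

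**Step 2: the CI-GABA correlation**

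If CI and GABA are linked only through age, the correlation between them is the product r(age, CI) × r(age, GABA). With n = 30 a sample correlation is significant at the 5% level when its absolute value exceeds 2.048 / sqrt(28 + 2.048²) = 0.36.

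The rejection rates below come from 40,000 simulated groups of 30 with age uniform on 18 to 55. The two age relations were given opposite signs; the rates are the same for equal signs.

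| Size of age correlation with each measure (assumed) | Size of induced correlation | Rejection rate, unadjusted | Rejection rate, adjusted for age |
|---|---|---|---|
| 0.2 | 0.04 | 5.4% | 5% |
| 0.3 | 0.09 | 7.6% | 5% |
| 0.4 | 0.16 | 13% | 5% |
| 0.5 | 0.25 | 26% | 5% |

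The inflation is negligible to slight up to 0.3 and becomes material from about 0.4 to 0.5. Partialling out age restores the nominal rate throughout.

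**The case against.** The strongest reply is that section 14.2 gives examples and does not close the list. Analysis of variance can carry covariates, correlation analysis can be partial, and a covariate list for secondary and exploratory work is often settled in a separate SAP, which is not at hand. This stands to a degree. A reader might infer that the sponsor has decided to leave the matching variables out; the protocol does not say so. But section 14.2 is itself headed as the statistical analysis plan, and its stated grounds for choosing a method are data type and distribution, not the matched design. Followed as written, it leads to unadjusted tests.

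A reader might also infer that the unadjusted contrasts with the controls are biased. The documents do not support that. Matching is meant to balance these variables between groups, and an unadjusted test after successful group matching is valid and, if anything, conservative. The loss is mainly one of efficiency. Some imbalance could remain: section 9.2.2 notes that some participants did not complete the RBANS, so the groups analysed may not be exactly the groups matched. Nothing in the protocol gives that a size or direction.

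Finally, a reader might infer that the baseline CI-GABA correlation is the plan's test of mechanism. Section 4.3 speaks of mutual validation for having two kinds of measure, just after noting the lack of longitudinal data, and its next paragraph speaks more modestly of further evidence. Section 14.2 presents the correlation as exploratory and within group. That limits the weight placed on it, but it does not remove the influence of age on the result.

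**Conclusion.** The point holds as a minor improvement to secondary and exploratory analyses. Section 14.2 names only unadjusted methods where a better one is available from variables that the matching already requires.

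- The gain in precision is a fall in the detectable difference from 0.72 to 0.69-0.61 SD for 30 v 30, or from 0.63 to 0.59-0.52 SD if the patient arms are pooled. It rests on the assumption that the matching variables explain 10-30% of within-group variance.
- The false-positive rate of the unadjusted CI-GABA correlation at n = 30 is about 5-8% for age correlations of 0.3 or less, 13% at 0.4 and 26% at 0.5. It rests on age being related equally strongly to both measures, which the protocol neither states nor excludes.

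The primary comparison of MST with ECT on YMRS is untouched.

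**What to change.** In section 14.2(1):

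- Specify a linear model (ANCOVA) with group and the matching variables for the baseline comparisons of MST, ECT and controls. Include at least age, sex and years of education, and either include socio-economic status or say why it is left out.
- Specify a partial correlation adjusted for age and sex for CI and GABA within each group.
- Report the unadjusted results as supportive.

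The cost is a change of wording and a few degrees of freedom. No new data are needed, since age, sex, education and socio-economic status must be recorded for the matching.

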### **5. Experimental Design: Randomized Controlled Study**

Randomization Method: A random number sequence will be generated and recorded by the computer, with each random number corresponding to a specific group (A for ECT group or B for MST group). Patients meeting the inclusion criteria will be assigned to either Group A or Group B based on the random number corresponding to their serial number.

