### **6. Participants**

This study plans to recruit 60 patients with bipolar manic for receiving MST and ECT treatments. Additionally, 30 healthy controls will be recruited without any intervention.

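### Baseline analyses in 14.2(1) keep the two randomised arms apart and state no pooled-patient contrast or CI-GABA correlation, which is inefficient for the mechanistic questions

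*Protocol*

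**What the plan says.** Protocol section 14.2, item (1), sets the baseline comparison of neurocognition, "CI indicators, and resting-state fMRI measures between the MST group, ECT group" and the healthy controls. The same item explores the correlation between CI indicators and GABA "levels detected within each group". As the three groups have just been listed, the natural reading is one correlation in MST patients, one in ECT patients and one in controls. The methods named in 14.2 are t-"tests, analysis of variance, and correlation analysis based on the data types and" distribution, given as examples. No analysis that combines the two patient arms at baseline is mentioned.

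The numbers come from sections 6 and 7: "This study plans to recruit 60 patients with bipolar manic for receiving MST and ECT treatments"; "30 healthy controls will be recruited without any intervention"; and "The sample size is 30 for ECT and MST group, respectively". Section 5 allocates patients by a computer-generated sequence, "each random number corresponding to a specific group (A for ECT group or B for MST group").

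The scientific questions are worded for patients as a whole. Section 4.3 speaks of an inhibitory deficit in bipolar patients and expects the TMS and MRS measures to support each other. Section 6.1 matches controls to a single patient group and assesses them at baseline only. The fMRI hypothesis in 14.2(3) is that patients "with bipolar mania may show enhanced connectivity within the DMN, and this" connectivity will improve after either treatment.

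**The concern.** At baseline nobody has been treated. Randomisation makes the MST and ECT arms two samples from the same population, so a baseline difference between them can only be due to chance. A three-group overall test spends one of its two degrees of freedom on that difference. Testing each arm against controls uses 30 patients at a time for a question that 60 can answer. Separate CI-GABA correlations have the same weakness, with no between-arm question to justify them.

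Two things are at stake. One is power for analyses that serve objectives 2 and 3 and are the main use of the 30 controls. The other is interpretation: with modest power in each arm, one arm may well show a significant correlation and the other not, and this could be misread as a difference between two groups that are exchangeable at that point.

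**Working it through.** **Inputs.** From the Protocol: 60 patients and 30 controls (section 6), 30 patients per arm (section 7), random allocation (section 5). Assumed: two-sided 0.05 for the baseline tests, complete data, a common SD, and no true MST-ECT difference before treatment. The Protocol gives no patient-control difference and no CI-GABA correlation, so ranges are used: standardised mean difference (SMD) d = 0.3 to 0.8 and r = 0.2 to 0.5.

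**The plan's own figure.** None is given for these baseline analyses. The 30 per arm in section 7 belongs to the treatment comparison. It cannot be reproduced, because the response rate and the margin in its formula are not stated. It is taken here as given.

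**Precision of the patient-control difference, in SD units.**
- One arm against controls: √(1/30 + 1/30) = 0.258.
- All patients against controls: √(1/60 + 1/30) = 0.224.
- Variance ratio: (1/60 + 1/30)/(1/30 + 1/30) = 0.75, a 25% reduction.

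**Power for means.**
- One arm v controls: noncentral t, 58 df, noncentrality d·√(30·30/60) = d·√15.
- Three-group test: noncentral F, 2 and 87 df, noncentrality d²·(60·30/90) = 20d².
- Pooled: noncentral t, 88 df, noncentrality d·√20.

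| SMD | One arm v controls | Three-group F | Pooled 60 v 30 | Pooled minus F (points) |
|---|---|---|---|---|
| 0.3 | 20.8% | 20.1% | 26.4% | 6.3 |
| 0.4 | 33.2% | 33.0% | 42.5% | 9.5 |
| 0.5 | 47.8% | 48.9% | 59.9% | 11.0 |
| 0.6 | 62.8% | 65.2% | 75.6% | 10.4 |
| 0.7 | 76.0% | 79.3% | 87.2% | 7.9 |
| 0.8 | 86.1% | 89.3% | 94.3% | 5.0 |

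The SMD detectable with 80% power is 0.74 for one arm v controls, 0.71 for the three-group F and 0.63 pooled.

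**The same contrast inside the three-group model.** A 1-df contrast of patients against controls, with 87 error df, has power 59.9% at SMD 0.5 and 75.6% at 0.6. These equal the pooled test to the precision shown.

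**Correlations (Fisher z).** Power is Φ(atanh(r)·√(n−3) − 1.96).

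| r | n = 30 | n = 60 |
|---|---|---|
| 0.2 | 18.2% | 33.4% |
| 0.3 | 36.3% | 64.7% |
| 0.4 | 59.5% | 89.2% |
| 0.5 | 81.4% | 98.6% |

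- Detectable with 80% power: tanh(2.802/√27) = 0.492 at n = 30 and tanh(2.802/√57) = 0.355 at n = 60.
- 95% interval around an observed r of 0.3: −0.068 to 0.596 at n = 30, and 0.050 to 0.515 at n = 60.
- Chance that exactly one of two exchangeable arms is significant at a true r of 0.4: 2 × 0.595 × 0.405 = 0.48.

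**The case against.** The strongest reply is that naming three groups loses nothing in itself. A three-group model uses all 90 people, and the 1-df contrast shown above recovers the pooled power for means. The loss arises only if the analyst relies on the overall F or on arm-by-arm tests. Section 14.2 prescribes neither: its methods are examples, and the choice of contrast is often left to a statistical analysis plan, which is not at hand. This stands. A reader might infer that the plan throws information away or necessarily halves the patient sample in every comparison with controls. The documents do not support that.

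For the correlations the reply is weaker, since the Protocol itself sets them within each group. Two within-arm estimates could be combined by Fisher z, with a detectable r of tanh(2.802/√54) = 0.364, close to the pooled 0.355. That combination is not excluded, but it is not stated either. The reduction is a single split from 60 to 30, the same split as for the means and not a further one.

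It is also fair that these analyses are secondary, that the correlation is introduced as exploratory, and that pooling can be adopted without new data. The arms can differ at baseline by chance, which is a reason to display them but not to analyse them apart.

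**Conclusion.** The point holds as one of efficiency and clear specification in the baseline mechanistic analyses. The gain from pooling is moderate for means: about 5 to 11 points of power over the three-group F for SMDs of 0.3 to 0.8. It is larger for correlations: about 15 to 30 points for r between 0.2 and 0.5, with the detectable correlation falling from about 0.49 to 0.355. These sizes rest on assumed effects, two-sided 0.05 and complete data. Section 9.2.2 reports that some participants did not complete RBANS, so the real numbers for that measure will be lower in every group.

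The primary YMRS comparison between MST and ECT is untouched. The argument gives no reason to add a patient-control comparison of GABA, which 14.2(1) does not list, or adjustment for the matching variables. Those would need their own justification.

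**What to change.** In 14.2(1):
- Prespecify the comparison of all 60 patients with the 30 controls for neurocognition, CI and resting-state fMRI, or equivalently the 1-df patients-versus-controls contrast in the three-group model.
- Estimate the CI-GABA correlation in all patients together and separately in controls.
- Show MST and ECT baseline values descriptively.

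Keep the arms separate for treatment-related change in 14.2(2).

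The cost is a few sentences in the plan. No additional patients, visits or measurements are needed.
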